### Sample size calculation

The sample size will be calculated based on previous studies conducted by Zhao Y et al. [14, 25]. A sample size of 420 patients will provide 80% power (α = 0.05) to detect a non-inferiority effect of EA therapy on the primary outcome, assuming a 10% loss. The non-inferiority margin will be 50% of the comparative efficacy between SA and solifenacin. The non-inferiority margin will be set based on our hypothesis that EA will be associated with at least 50% of the difference in efficacy of solifenacin compared with SA.

### Measures to improve compliance

Establishing a good relationship between doctors and patients, and providing participants with subsidies for transportation costs. A patient manual for regular short message services will be used to remind patients to complete the bladder diary.

### Statistical analysis

Statistical analysis will be conducted by independent third-party professional statisticians. We will use a modified t-test based on the retention of the effect method to analyse whether EA is non-inferior to solifenacin [26]. If the lower boundary of the confidence interval around the mean difference between the numbers in the EA group versus the solifenacin group exceed 50% of the mean difference between the numbers in the solifenacin group and the SA group, then non-inferiority will be claimed. The intention-to-treat (ITT, randomized participants) and per-protocol datasets (PP, ITT participants who received at least one treatment session) will be used to analyse the primary outcome. Missing data will be filled with a multiple imputation method under the missing-at-random assumption. Secondary outcomes will be calculated with observed values. Categorical data will be described by case number and percentage and will be analysed with Fisher’s exact test or the Chi-square test where appropriate. Continuous data will be described as the mean ± standard deviation, median, maximum and minimum values, and comparisons between groups will be conducted by covariance analysis or nonparametric tests where appropriate. A P (2-tailed) value less than or equal to 0.05 will be considered statistically significant. Statistical Package for the Social Sciences (version 13.0; SPSS; Chicago, Illinois, USA) will be used to perform the statistical analysis.

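### The plan gives two non-equivalent rules for its one primary decision: the EA–solifenacin interval rule is not the retention-of-effect test it names and, direction fault aside, is more conservative and less powerful

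*Protocol article*

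**What the plan says.** The Statistical analysis section names the primary test: "We will use a modified t-test based on the retention of the effect method to analyse whether EA is non-inferior to solifenacin". Table 1 also lists a modified t-test, and nothing else, for the primary outcome.

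The following sentence states when the claim is made. The quantity it judges is "the lower boundary of the confidence interval around the mean difference between the numbers in the EA group versus the solifenacin group". That interval covers two arms, EA and solifenacin. The threshold is half of the solifenacin–SA mean difference observed in the trial's own groups; in the article's words, the limit must "exceed 50% of the mean difference between the numbers in the solifenacin group and the SA group, then non-inferiority will be claimed".

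The Sample size calculation section defines the margin in the same relative way, "The non-inferiority margin will be 50% of the comparative efficacy between SA and solifenacin", and describes the hypothesis as EA keeping at least half of solifenacin's advantage over SA. It states: "A sample size of 420 patients will provide 80% power (α = 0.05) to detect a non-inferiority effect of EA therapy". The allowance for dropout is given in the same sentence as "assuming a 10% loss". It gives no effect size, SD or numeric margin, and does not say which of the two rules the power belongs to. The level of the confidence interval is not stated either; the Statistical analysis section gives only a general two-tailed threshold of 0.05.

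**The concern.** Keeping at least half of solifenacin's effect means EA − SA ≥ 0.5·(Sol − SA), that is, EA − 0.5·Sol − 0.5·SA ≥ 0. This is a three-arm contrast, and a retention-of-effect test uses the standard error of that contrast. The interval rule uses the standard error of EA − Sol alone. It treats the margin as known, although the margin is estimated from the same patients and is correlated with EA − Sol through the shared solifenacin arm.

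The article therefore commits to two rules for one decision, and they can disagree on the same data. A choice between them could then be made after the results are seen. If the sample size was worked out for one rule and the claim is made by the other, the stated power is not the power of the decision.

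**Working it through.** **Inputs**
- Retention fraction 0.5 (Sample size calculation).
- Allocation 1:1:1, 140 per arm; with 10% loss 140 × 0.9 = 126 evaluable per arm (Study design; Sample size calculation).
- Two-tailed 0.05 (Statistical analysis), read here as a two-sided 95% interval. This is an assumption; a 90% interval is shown as the alternative.
- Equal SD σ in the three arms. This is an assumption and is varied below.
- Benefit scored positive, so that a larger value means a larger fall in OABSS.

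**The plan's own figure.** The loss step is consistent (126/0.9 = 140). The 420 itself cannot be reproduced, because no effect size, SD or numeric margin is given. The comparison below does not need them.

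**Direction.** As written, the lower limit for EA − Sol must exceed plus half of the solifenacin–SA difference. With benefit positive, this demands superiority by half the drug effect; power is about 0.05% when EA equals solifenacin and the named test has 80%. With raw OABSS change, where a fall is benefit, the lower limit is the wrong limit. That is a separate fault and is corrected here, so that what remains can be seen.

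**The two rules**
- Named test: EA − 0.5·Sol − 0.5·SA > z·σ·√(1.5/n), since 1 + 0.25 + 0.25 = 1.5.
- Interval rule: EA − Sol − z·σ·√(2/n) > −0.5·(Sol − SA), which rearranges to EA − 0.5·Sol − 0.5·SA > z·σ·√(2/n).

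The left-hand sides are identical. The cut-offs differ by √(2/1.5) = 1.1547.

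**Type I error of the interval rule**
- 95% interval: 1.1547 × 1.960 = 2.263, so the one-sided error is 1 − Φ(2.263) = 1.18% instead of 2.5%.
- 90% interval: 1.1547 × 1.645 = 1.899, so the one-sided error is 2.9% instead of 5%.

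**Power, by what 420 was sized for**

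| Sizing basis | Interval used | Named test | Interval rule |
|---|---|---|---|
| Named test, one-sided 2.5% | 95% | 80% | Φ(1.960 + 0.842 − 2.263) = 70.5% |
| Named test, one-sided 5% | 90% | 80% | 72.1% |
| Named test, one-sided 5% | 95% | 70.1% | 58.8% |
| Fixed-margin formula, one-sided 2.5% | 95% | 90% | 83% |

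The loss in these rows runs from about 6 to 11 points. At the 95% level it cannot exceed 2Φ((2.263 − 1.960)/2) − 1 ≈ 12 points.

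**In the first row**, the named test succeeds and the interval rule fails in about 9.5% of trials (80% − 70.5%). Restoring 80% under the interval rule would need ((2.263 + 0.842)/2.802)² = 1.23 times the patients. A simulation with t critical values at 126 per arm (400,000 runs) gave error 1.19% against 2.44%, and power 70.1% against 79.8%.

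**Unequal SDs.** With one arm's SD changed (EA or SA to 0.8 or 1.25 times the others, solifenacin to 1.25 times), the interval rule's error is 0.7% to 1.5% and its power 64% to 74%, against 2.5% and 80%.

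**The case against.** The strongest reply is that the interval sentence is only a loose gloss on the named test. Table 1, the sentence naming the test and the retention hypothesis in the sample size section all agree, and a sentence with a direction fault is weak evidence that the statisticians would use the two-arm standard error. A condensed article could leave the formula to the analysis plan. This does not remove the point: the article does not leave the rule open but prints one, and an interval for EA versus solifenacin cannot carry the variance of the three-arm contrast. Followed as written with only the direction repaired, it gives a different verdict in some trials.

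Three parts of the reply do stand.

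- A reader might infer that the rule simply runs at 1.2% error and 70% power, so that the stated 80% is not met. The documents do not support that as fact. The interval level, the SDs and the basis of the 420 are not given, and under a fixed-margin formula the interval rule has about 83%, with no shortfall against 80%. The 23% increase in patients falls away in that case too.
- A reader might infer a risk of excess false claims. The opposite holds: with a common SD, any result that passes the interval rule also passes the named test at the same z.
- Replacing the rule by the contrast alone would be incomplete. The contrast can be positive when solifenacin is no better than SA, and keeping half of its effect then has no meaning.

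**Conclusion.** The concern holds as an inconsistency in the primary decision rule. The named test and the printed claim rule share a statistic but not a standard error, and the printed rule is the wrong one for the stated hypothesis. Under equal SDs and 1:1:1 allocation, and apart from the direction fault, its cut-off is 15% too large and its one-sided error is about half the nominal level. That much does not depend on the effect size or on the size of a common SD.

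The power cost is certain in direction. Its size is conditional: roughly 6 to 12 points, with the level reached depending on how 420 was derived. The consequences are avoidable loss of power and an ambiguous verdict on the only primary outcome. Whether the stated 80% is missed cannot be settled from the article.

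**What to change.** Replace the interval sentence in the Statistical analysis section with one rule: with benefit scored positive, non-inferiority is claimed if the lower limit of the two-sided 95% confidence interval of EA − 0.5·Sol − 0.5·SA, with that contrast's own standard error, is above 0. Add that this is interpreted as retention of effect only if solifenacin is shown to be better than SA in the trial. This wording also removes the direction fault.

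In the Sample size calculation section, state which test the 80% power and α = 0.05 refer to, and whether α is one-sided or two-sided. Report the EA–solifenacin confidence interval descriptively.

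The cost is wording in the protocol and analysis plan, with no further patients or data. If 420 was sized for the named test at one-sided 2.5%, the change keeps about 10 points of power that the printed rule would lose.

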#### Study design

This study will be a multi-centre, randomized, parallel group, and three-arm clinical trial. It will be conducted from September 2019 to June 2021 in 4 hospitals around China. If the study is not expected to be completed on time, 2 research hospitals will be added or replaced. Participants with OAB will be recruited via posters, television, websites and outpatients and will then be screened according to the eligibility criteria. A total of 420 participants will be ultimately enrolled. Prior to enrolment, all participants will voluntarily sign the informed consent form that has been approved by the ethics committee. Randomization will be performed centrally by the Clinical Evaluation Centre of the China Academy of Chinese Medical Sciences in Beijing, and eligible participants will be randomized to the EA group, sham electroacupuncture (SA) group or solifenacin group at a 1:1:1 allocation ratio. A randomization number will be applied after enrolment. The statisticians, outcome assessors, and participants in the EA and SA groups will be blinded to the allocation. A flowchart demonstrating an outline of the study is included in Fig. 1.

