### Randomization and blinding

After the 1-week assessment has been carried out and informed consent has been obtained, participants will be divided into the EA group, SA group or solifenacin group at a ratio of 1:1:1 due to the completely randomized block design of the hospital factor. Randomization will be generated by the central random system based on the computer network. Randomized numbers and groupings will be applied by research assistants who are not involved in the treatment or evaluation. Patients in the EA group and the SA group will be blinded, while those in the solifenacin group will be subjected to open trials. In the informed consent signed before the participants were enrolled, we will inform them that there are two types of acupuncture in addition to the drug group, and participants will be required to complete the entire trial cycle no matter which group they are assigned to. After the last treatment, the evaluation for the blinding of acupuncture will be tested within 5 min in the EA and SA groups. The results of this evaluation will be used to analyze the effect of blinding on the trial outcome measures. Efficacy evaluation and data entry will be performed by research assistants who are not involved in the grouping. The statisticians, outcome assessors, and physicians will be blinded to the allocation during data summarization.

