### Outcome measures

In this study, there will be one primary outcome and nine secondary outcomes. These are presented in Table 1. All adverse events will be recorded. The OABSS is widely used as a primary outcome measure in OAB studies, as it is safe and convenient and has been proven to have good reliability and validity in OAB [22]. The OABSS is comprised of 4 test items including frequency of urination, nocturia, urgency urinary incontinence and urgency episodes in 24 h. Total score ranges from 0 to 15, with scores of 3 to 5 indicating mild OAB, 6 to 11 indicating moderate OAB, and 12–15 indicating severe OAB. The secondary outcomes are based on 7-day bladder diaries and the OAB-q. A previous study suggested that 7-day bladder diary provided more accurate information regarding incontinence than a 3-day diary [23], in which we will evaluate the average episodes of 24 h urination, nocturia, urge incontinence and urgent urination changes from baseline. The OAB-q, with 33 questions about sleeping, anxiety, trouble in life and so on, is appropriate for assessing symptomatic distress or assessing the impact of OAB on health-related quality of life [24].

**Table 1 Tab1:** Outcome measures

	Outcome measure	Time point	Description	Statistics
Primary outcome	Change in OABSS from baseline to the end of week 12	Week 12	Calculated based on the OABSS.	Modified t-test
Secondary outcomes	Change in OABSS from baseline to the end of weeks 4, 8, 20, and 32	Weeks 4, 8, 20, and 32	Calculated in the same way as the primary outcome.	Covariance analysis or non-parametric test
	Proportion of participants with a decrease in the OABSS of ≥3	Weeks 4, 8, 12, 20, and 32	The number of patients with a reduction in OABSS ≥3 divided by the number of participants at baseline.	A chi-square test or Fisher’s test
	Change in 24 h urination/nocturia/urgency urinary incontinence /urgency episodes from baseline	Weeks 4, 8, 12, 20, and 32	The average 24 h urination/nocturia/urgency urinary incontinence /urgency episodes equal to the sum of urination/nocturia/urgency urinary incontinence/urgency episodes divided by 7.	Covariance analysis or non-parametric test
	Change in OABSS for each question from baseline	Weeks 4, 8, 12, 20, and 32	Calculated based on the OABSS for each question.	Covariance analysis or Non-parametric test
	Change in OAB-q from baseline	Weeks 4, 8, 12, 20, and 32	Calculated based on the OAB-q.	Covariance analysis or non-parametric test

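### The primary week-12 OABSS comparison is given a modified t-test with no covariate, a valid choice that gives up precision available from baseline OABSS and, to a lesser extent, hospital

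*Protocol article*

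**What the plan says.** Table 1 in the Outcome measures section of the protocol article defines the primary outcome as "Change in OABSS from baseline to the end of week 12" and puts "Modified t-test" in its statistics column. The Statistical analysis section repeats this, naming a "modified t-test based on the retention of the effect method" for the non-inferiority comparison of electroacupuncture with solifenacin. Neither place names a covariate or a stratum. The article explains the method only as retention of 50% of the solifenacin effect over sham.

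In the same table, OABSS change at weeks 4, 8, 20 and 32, the diary changes, the item-level OABSS changes and the OAB-q change are assigned "Covariance analysis or non-parametric test". The general rule for continuous data in the Statistical analysis section is that "comparisons between groups will be conducted by covariance analysis or nonparametric tests where appropriate". No covariates are named for these analyses either.

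The Inclusion criteria require an OABSS of at least 6, and the Procedure section lists baseline among the assessment times, so a baseline score exists for every patient. Under Randomization and blinding, allocation follows a "completely randomized block design of the hospital factor". The Study design section places the trial "in 4 hospitals around China", with two more to be added or substituted if recruitment is slow.

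**The concern.** A t-test on change treats the baseline score as if its slope on the week-12 score were exactly 1. ANCOVA estimates that slope from the data. Where the true slope differs from 1, the change score carries noise that the baseline could remove. Leaving hospital out also keeps any between-hospital variation in change within the error term, although randomisation was blocked on it.

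The primary test is where precision counts most. The trial is planned at 80% power, and the retention criterion uses all three arm means, so chance baseline differences enter both the electroacupuncture (EA) versus solifenacin comparison and the solifenacin versus sham electroacupuncture (SA) difference that sets the margin. Covariance analysis is already in the plan for the same score at other visits, and the article gives no reason for treating week 12 differently.

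**Working it through.** **Inputs from the article.** Total 420, 140 per arm, 1:1:1; 80% power; alpha 0.05; 10% loss; margin 50% of the solifenacin–SA difference. The Sample size calculation section does not say whether alpha is one- or two-sided. The Statistical analysis section uses two-tailed 0.05, so one-sided 0.025 is taken here.

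**Inputs assumed.** The correlation rho between baseline and week-12 OABSS, and k = baseline SD / week-12 SD. Neither is in the article. The range used is rho 0.3 to 0.7 and k 0.7 to 1.

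**The plan's own figure.** The loss allowance is consistent: 140 × 0.9 = 126 evaluable per arm. The total of 420 cannot be reproduced forward, because no SD and no expected solifenacin–SA difference are given. Working backwards, with improvement scored as positive, retention of half the effect means EA − 0.5·solifenacin − 0.5·SA > 0. The variance of this contrast is (1 + 0.25 + 0.25)·SD²/n = 1.5·SD²/n. If EA truly equals solifenacin, 80% power at one-sided 0.025 needs a solifenacin–SA difference of √(1.5/126) × 2.8016 / 0.5 = 0.61 SD of change.

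**Variance of the two analyses.** Set the week-12 SD to 1.

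- Change score: 1 + k² − 2·rho·k
- ANCOVA residual: 1 − rho²
- Difference: (k − rho)², which is never negative
- Ratio, ANCOVA to change: R = (1 − rho²) / (1 + k² − 2·rho·k)

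Apart from a trivial loss of degrees of freedom, ANCOVA is therefore never less precise, and the gain is nil when k = rho. If k = 1 the ratio reduces to (1 + rho)/2. The factor 1.5/n is common to both analyses, so R carries over to the retention contrast.

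**Power.** If the t-test on change has 80% power, power after baseline adjustment is Φ(2.8016/√R − 1.96).

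| k | rho 0.3 | rho 0.5 | rho 0.7 |
|---|---|---|---|
| 1.0 | R 0.65, 93.5% | R 0.75, 89.9% | R 0.85, 86.0% |
| 0.8 | R 0.78, 88.6% | R 0.89, 84.3% | R 0.98, 80.8% |
| 0.7 | R 0.85, 85.9% | R 0.95, 82.0% | R 1.00, 80.0% |

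Example, k = 0.8 and rho = 0.3: R = 0.91/1.16 = 0.784, and Φ(2.8016/0.886 − 1.96) = Φ(1.20) = 88.6%.

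A simulation of the three-arm contrast at k = 1 (126 per arm, 5,000 runs per rho) gave 80.0%, 80.5% and 79.1% for the t-test on change, and 93.2%, 89.8% and 85.5% for ANCOVA, at rho 0.3, 0.5 and 0.7. At one-sided 0.05 the k = 1 row becomes 92.5%, 89.0% and 85.4%.

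**Hospital.** If hospital explained 2%, 5% or 10% of the variance of change (assumed shares), adjusting for it alone would move power from 80% to 80.8%, 82.0% or 84.0%.

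**The case against.** The strongest reply is that a pre-specified t-test on change is a sound primary analysis. That stands. A reader might infer that regression to the mean, after selecting patients at OABSS 6 or above, biases the result. It does not: it is expected equally in all three randomised arms and distorts no contrast between them. Ignoring the hospital blocking tends to make the standard error too large, which does not favour a false claim of non-inferiority. If the sample size was based on the SD of change, the planned 80% power holds without adjustment.

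A reader might also take the equal-SD row as the size of the loss, where R = 0.65 at rho 0.3 amounts to 1/0.65 = 1.54, or 54% more patients. The article does not support that. Entry at 6 or above on a 0 to 15 scale truncates the baseline distribution, while week-12 scores can fall to 0, so k may well be below 1. Nor is it true in general that adjustment gains whenever the correlation is below 1; at k = rho it gains nothing. For hospital, stable differences between centres in OABSS level already cancel in a change score, so little may remain.

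Finally, the absence of adjustment is inferred. The test is defined by a cited source that is not at hand, and a fuller plan could add covariates. The secondary outcomes are promised covariance analysis only as one of two options. These points temper the wording. They do not remove the issue: the article twice names the primary method without adjustment, describes its modification as effect retention, and sets it apart in Table 1 from the covariance analyses.

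**Conclusion.** The point holds as a matter of efficiency. The stated primary test is valid and unbiased, but it forgoes precision that baseline OABSS could supply at the one comparison on which the conclusion rests. Over rho 0.3 to 0.7 and k 0.7 to 1, at one-sided 0.025 and from a starting power of 80%, the gain runs from about nil (80.0%) to 13.5 points (93.5%). Where in that range this trial lies cannot be told from the article. Hospital adjustment probably adds little power; its main merit is that the analysis then matches the blocked randomisation. This is a recommended improvement and not the correction of an error.

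**What to change.** In Table 1 and the Statistical analysis section, make the primary analysis an ANCOVA of week-12 OABSS change with treatment (three arms), baseline OABSS and hospital. Test the contrast EA − 0.5·solifenacin − 0.5·SA of the adjusted means, with improvement scored as positive, against 0 using its lower confidence limit. This keeps the 50% retention criterion. Fit the model within each imputed data set, since multiple imputation is already planned, and combine the results by Rubin's rules. Keep the modified t-test as a sensitivity analysis.

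No new data are needed and the sample size need not change. The cost is a documented change to the primary method of a registered trial that was already recruiting (23 participants according to the Trial status section). It should be recorded as a dated change made before unblinding.

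### The printed non-inferiority rule has the wrong sign: as written, it either requires EA to beat solifenacin or passes an EA no better than sham

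*Protocol article*

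**What the plan says.** The protocol states the margin in words in the Sample size calculation section: "The non-inferiority margin will be 50% of the comparative efficacy between SA and solifenacin". It gives the reason as the hypothesis that "EA will be associated with at least 50% of the difference in efficacy of solifenacin compared with SA".

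The Statistical analysis section names the method: "We will use a modified t-test based on the retention of the effect method to analyse whether EA is non-inferior to solifenacin". It then gives the decision rule in one sentence, which begins "If the lower boundary of the confidence interval around the mean difference between the numbers in the EA group versus the solifenacin group" and ends "exceed 50% of the mean difference between the numbers in the solifenacin group and the SA group, then non-inferiority will be claimed".

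The primary outcome in Table 1 is "Change in OABSS from baseline to the end of week 12". Higher OABSS is worse: "Total score ranges from 0 to 15, with scores of 3 to 5 indicating mild OAB", with higher bands for moderate and severe disease. Nowhere does the article say whether change is counted as a reduction (positive = better) or as week 12 minus baseline (negative = better).

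**The concern.** The two sections give different conditions for the same claim. Retaining at least half of solifenacin's effect allows EA to be somewhat worse than the drug, so the bar for EA − Sol has to lie on the unfavourable side of zero. The printed rule puts the bar at plus half of Sol − SA, with no minus sign. Because the coding of change is open, the fault can act in either direction: it can block a claim the trial ought to make, or allow one it ought not to make. This is the only decision rule printed for the primary outcome, and the trial's main conclusion rests on it.

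**Working it through.** **Inputs.** From the protocol: 420 patients, 1:1:1, 10% loss, 80% power, α = 0.05, 50% retention. The general significance level is two-tailed 0.05; the interval level for the non-inferiority test is not stated, so I assume a two-sided 95% interval. No effect size or SD is printed.

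**The plan's own figure.** Only the loss adjustment can be reproduced: 126 / 0.9 = 140 per arm, and 3 × 140 = 420. The power claim can be neither confirmed nor refuted.

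**Algebra.** Write EA, Sol and SA for the mean changes, and D > 0 for solifenacin's true benefit over sham.

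- Intended, with improvement positive: EA − SA ≥ 0.5(Sol − SA). Subtracting (Sol − SA) from both sides gives EA − Sol ≥ −0.5(Sol − SA), or EA − 0.5 Sol − 0.5 SA ≥ 0.
- As written: lower limit of (EA − Sol) > +0.5(Sol − SA).
- Reduction coded positive: Sol − SA = D, so the rule needs EA − Sol > +D/2. EA must reach more than 1.5 times the drug's effect.
- Week 12 minus baseline: Sol − SA = −D, so the rule needs EA − Sol > −D/2. A larger EA − Sol now means a worse EA. An EA equal to sham has EA − Sol = +D and passes.

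There are eight readings (two codings, two subtraction orders for each difference). Two give the intended rule, and each needs one difference taken against its written order: SA − Sol with reduction coding, or Sol − EA with week 12 minus baseline.

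**Assumed effect.** The contrast EA − 0.5 Sol − 0.5 SA has variance 1.5 SD²/n. With n = 126 and SD = 1, its standard error is √(1.5/126) = 0.1091. Power of 80% at EA = Sol needs D/2 = (1.960 + 0.842) × 0.1091 = 0.3057, so D = 0.611 SD.

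**Probability of a claim under the written rule.** The governing quantity is EA − 1.5 Sol + 0.5 SA, with standard error √(3.5/126) = 0.1667. If the EA − Sol interval is compared with the estimated half-difference, a claim needs this quantity to exceed 1.96 × √(2/126) = 0.247.

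- Reduction coding, EA = Sol: mean −0.306; z = (−0.306 − 0.247)/0.1667 = −3.32; probability 0.05%.
- Week 12 minus baseline, EA = SA: mean +0.917; z = (0.917 − 0.247)/0.1667 = 4.02; probability above 99.9%.
- Week 12 minus baseline, EA keeping exactly half: mean +0.611; z = (0.611 − 0.247)/0.1667 = 2.18; probability 98.6%.

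The written rule can also be tested as a full contrast, with threshold 1.96 × 0.1667 = 0.327. In the table, the first figure in each pair is the interval comparison and the second is the full contrast.

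| True EA effect | Intended contrast test | Written rule, reduction positive | Written rule, week 12 minus baseline |
|---|---|---|---|
| EA = SA | <0.01% | <0.01% / <0.01% | >99.9% / 99.98% |
| Half the drug effect | 2.5% | <0.01% / <0.01% | 98.6% / 95.6% |
| EA = Sol | 80% | 0.05% / 0.01% | 64% / 45% |
| Twice the drug effect | >99.9% | 64% / 45% | 0.05% / 0.01% |

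**Range over the assumed effect, same order of figures.**

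- D = 0.3 SD: reduction coding at EA = Sol, 0.9% / 0.2%; week 12 minus baseline at EA = SA, 89% / 77%, and with EA keeping exactly half, 62% / 44%.
- D = 0.8 SD: below 0.01% in the first case and essentially 100% in the second.
- One-sided 0.05 (D = 0.543 SD for 80% power), full contrast: 0.05% and 99.9%.

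**The case against.** The best defence is that this is a slip of wording. The Sample size calculation section states the hypothesis correctly, and the named retention-of-effect test carries its own direction. A difference between two groups does not strictly fix a subtraction order, and the Sample size calculation section names the same margin with sham first. Read as SA − Sol on an improvement scale, the sentence is right. The cues also lean towards improvement coding: the margin is described as efficacy, the responder outcome counts reductions, and the rule tests a lower limit. In that case the literal error is conservative and cannot pass an ineffective EA.

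Much of this stands. A slip is the likeliest explanation, and the false-claim branch depends on a coding that the protocol does not state. The probabilities rest on a back-solved effect and vary with the standard error. The 80% and 2.5% comparators belong to the contrast test; correcting only the sign while comparing the EA − Sol interval with an estimated margin gives 70% and 1.2%.

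None of it rescues the sentence. The favourable reading must reverse one of the two differences, and nothing printed tells the outside statisticians to do so. If the named test governs, the sentence contradicts that test. A separate analysis plan may have the rule right, but it would then conflict with the published protocol.

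**Conclusion.** The concern holds. With both differences taken in the order written, the rule is wrong under either coding of change and contradicts the protocol's own hypothesis. That conclusion is algebraic and needs no effect size or SD.

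The size of the consequence rests on 126 evaluable patients per arm, equal SDs, a normal approximation and an assumed solifenacin effect. Across 0.3 to 0.8 SD and both ways of forming the standard error, at a two-sided 95% level, the written rule gives at most a 0.9% chance of a claim when EA equals solifenacin (improvement positive). It gives at least a 77% chance when EA equals sham (week 12 minus baseline). It must be corrected before the primary analysis.

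**What to change.** Replace the decision sentence in the Statistical analysis section with wording such as: *Change is defined as baseline minus week 12, so that positive values mean improvement. Non-inferiority is claimed if the lower limit of the two-sided 95% confidence interval for EA − 0.5 × solifenacin − 0.5 × SA is above 0.* In terms of true means, this says that EA − Sol exceeds minus half of Sol − SA. State the contrast form as the rule, because setting an EA − Sol interval against an estimated margin is a different test with different error rates.

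State the coding of change once, in Table 1, and check that the analysis plan, which was not available here, carries the same rule.

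The cost is one sentence and one coding statement, with no effect on conduct. The Trial status section reports 23 recruits, so a correction at that stage is clean prespecification. Choosing the sign after the results are known would leave the primary claim open to challenge.
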